#### Secondary outcomes

2.12.2

The secondary outcomes for the study include anthropometric measures including waist circumference (WC), hip circumferences (HC), waist to hip ratio (WHR), and waist to height ratio (WhTR), and NCD risk factors awareness (45).

### Conceptual framework

2.13

The study will incorporate the Socio-ecological model (SEM) in its qualitative inquiry to identify the barriers and facilitators to the adoption of lifestyle modification. The model provides a holistic approach to understand how personal, inter-personal, social, organizational, and physical environments plays a role in shaping one’s health related behavior. This model is also helpful in navigating health policies, as it highlights the components that most influence health and lifestyle choices (46). The model divides the determinants of health behavior into 4 levels; individual factors such as knowledge, inter-personal factors including relationships with family and peers, community factors such as access to healthy foods, and policy level such as access to gyms at workplaces. Using the SEM model helps target multiple levels of health behavior and can identify which ones have the most impact, as either a barrier or a facilitator, in adopting healthier lifestyle beyond the individual level (47).

In addition to the SEM, the intervention will be guided by the Trans-Theoretical Model (TTM). The TTM helps guide participant engagement and facilitates behavior change. The model views behavior change as dynamic process spanning over 5 distinct stages including, pre-contemplation, contemplation, preparation, action, and maintenance. The TTM states that for an individual to achieve sustainable behavior change, he/she must go through each stage or else there may be a significant risk of relapse. Tailoring the interventions according to the participants’ degree of readiness increases chances of success. The TTM further allows for individualized and stage appropriate guidance which enhances intervention effectiveness and sustainability (48). Additionally, in group based interventions, TTM has proven to be effective as it facilitates peer support while simultaneously allowing for individual reflection. TTM acknowledges that behavior change is gradual and non-linear, therefore it is flexible, theoretically grounded, and participant focused. These attributes help improve the relevance and implementation feasibility of public health interventions (49).

### Data analysis plan

2.14

The data collected will be analyzed via SPSS version 26. The confidence interval will be set at 95%, hence *p* value of less than 0.05 will be considered significant in the findings. The data analysis plan is shown in Figure 4.

**Figure 4 fig4:**
[figure not shown]
Quantitative data analysis plan: this figure includes a summary of the descriptive and inferential quantitative data analysis plan.

#### Descriptive statistics

2.14.1

Data will be analyzed using frequencies, percentages to report the prevalence and proportion of NCD risk factors and their associated knowledge and attitudes in the study population. A comparative analysis will be done between the baseline and end line data to study the influence of our study’s intervention in reducing the NCD risk factors and improving the knowledge and practices regarding them and their contributing behaviors.

#### Inferential statistics

2.14.2

Paired samples t-test will be used to compare the pre and post intervention values of continuous variablesMcNemar test will be used to compare the pre and post intervention values of categorical variablesChi-square test will be applied to determine associations between different variablesRegression analysis will be conducted to estimate the direction and strengths of relationships between independent and dependent variablesTo adjust for potential confounders such as socio-demographic variables, multivariable regression models will be employed. Variables such as age, household income, education level, will be included as covariates in the DiD analysis. This will help adjust for baseline differences between control and intervention groups, ensuring more accurate attribution of the intervention’s effects. This further enhances the internal validity of the study via limiting confounding bias.To control the risk of type I error, statistical corrections will be applied for multiple comparisons, where appropriate. This will include Bonferroni correction and/or false discovery rate (FDR) correction.

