
#### Phase 2: intervention development and implementation

2.2.2

The intervention phase will involve exposing the intervention group to nutrition and physical activity knowledge in the form of educational sessions, which will be divided into 12 sessions. Three sessions will be given each month for the first 6 months, and two sessions will be given each month for the last 3 months. The intervention sessions will be delivered by trained health professionals including registered dietitians, and physical fitness experts. The intervention will be delivered in a group format where the participants will receive joint counseling. However, participants will be encouraged to seek individualized guidance during or after sessions, to address any personal concerns. Individualized diet plans may also be administered to participants with special needs or multiple risk factors. This will ensure tailored support within a group-based framework.

Nutrition intervention—will comprise of bimonthly education and counseling sessions on healthy food choices, identifying and reducing intakes of unhealthy foods, equipping participants to prepare healthy meals from the foods available at home, self-monitoring of eating habits and NCD risk factors, and incorporating nutrition guidelines from Pakistan Dietary Guidelines for Better Nutrition (PDGN) into daily life. A total of 12 sessions will cover important nutrition topics to increase participant awareness of healthy diets and individual diet plan provision will help them guide them in their daily nutrient intake. The topics for these sessions are given below:Physical activity intervention—will include physical activity education and training sessions as per the Pakistan Dietary Guidelines for Better Nutrition (PDGN) recommendations, and WHO physical activity guidelines. One session per 15 days will be done and participants will be guided on how to incorporate physical activity in their daily routine. Aerobic exercises such as walking and jogging will be promoted and the use of pedometers will be encouraged to count daily steps. Each participant will be advised to walk at least 30 min every day for a minimum of 5 days a week as per WHO guidelines.

The topics for these sessions are given in Figures 2, 3.

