The control group will go about their usual routine and will receive no nutrition or physical activity related sessions or educational material during the study period. Once the study has concluded they will be given lifestyle intervention sessions as an ethical consideration. However, to ensure consistency in data collection and monitoring, the control group will undergo standardized follow-up assessments at the same time frames as the intervention group (baseline and endline). Additionally, monitoring visits will be conducted at the control group schools to ensure engagement, minimize attrition, and warrant consistent study conditions. Lastly, fidelity checks will be conducted during data collection, by research supervisors, to ensure standardized administration of questionnaires and anthropometric measurements.

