#### Stage 1: selecting schools

2.7.1

Defining clusters: all public schools within Islamabad city will be considered clusters.Sampling frame: list of all public schools in Islamabad city will be the sampling frame and will be obtained from the education department.Number of schools selected: according to Pakistan Education Statistics report (2021–22) 15 teachers on average in each school – 130/15 = 8 schools selected via purposive sampling. Purposive sampling was chosen to select schools based on practical considerations such as administrative permissions and accessibility, institutional cooperation, and the practicality of implementing a lifestyle intervention in real-world school settings. This will enhance the study’s contextual relevance, and help understand the feasibility of future up-scaling within similar environments (39). Employing purposive sampling may limit the study’s applicability to other population groups such as private or rural school teachers. However, utilizing purposive sampling will help prioritize contextual comprehension and intervention feasibility at a deeper level. This is consistent with implementation research frameworks that prioritize situational understanding over statistical representativeness (40).

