### Sample size calculation

2.8

The sample size is calculated on the basis of BMI reported from a similar study conducted in India (41) using the formula: $n=[2\times (\sigma^{2})\times {\left(Z₁-\alpha /₂+Z₁-\beta \right)}^{2}]/d^{2}$

Where SD = 0.96.

Alpha = 0.05.

Power of study = 80%.

Effect size = 0.5.

Non-response rate = 10%.

Sample size = 65 per group and total sample = 130 teachers (both groups).

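### If whole schools form the arms, as most of the protocol indicates, the named analyses ignore within-school correlation and the 5% level does not hold; the unit of allocation must be settled first

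*Protocol article*

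**What the plan says.** **Design.** Section 2.7 describes two-stage cluster sampling. In section 2.7.1, "all public schools within Islamabad city will be considered clusters", and eight schools are chosen purposively from an average of 15 teachers per school. In section 2.2.2, "The intervention will be delivered in a group format", and the paragraph on the control group says that "monitoring visits will be conducted at the control group schools". Section 2.1 calls the study quasi-experimental. Section 2.7.2, however, says that eligible teachers are drawn by lottery into the intervention or the control arm. No section states outright that each school belongs to one arm.

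**Analysis.** Section 2.14.2 lists paired t-tests and McNemar tests for pre-post comparisons, chi-square tests for associations, and regression. For the DiD analysis it says that "multivariable regression models will be employed. Variables such as age, household income, education level, will be included as covariates in the DiD analysis". The only protection of the type I error named is Bonferroni or false discovery rate correction. Section 2.14.1 presents the baseline to end-line comparison as the way to study the influence of the intervention. Section 2.14 fixes the level: "The confidence interval will be set at 95" per cent, with p below 0.05 taken as significant.

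**Sample size.** Section 2.8 uses the formula for two independent means with SD 0.96, "Power of study = 80" per cent, "Effect size = 0.5" and "Non-response rate = 10" per cent, giving 65 per group.

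**The concern.** Teachers in one school share a principal, a timetable, colleagues and, in the intervention arm, the sessions themselves. Their changes in BMI, diet, activity or awareness are therefore likely to be correlated. If each school sits wholly in one arm, the arm contrast carries the school-to-school variation in change, and with eight schools little of it averages out. A regression that treats teachers as independent leaves this out of the standard error. Age, income and education are teacher-level covariates and do not put it back. Bonferroni or false discovery rate correction deals with the number of tests, not with p-values that are each too small.

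At stake is the main claim of the study. A significant DiD estimate could be ordinary variation between a handful of schools, yet the Conclusion expects the findings to inform policy and scale-up.

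**Working it through.** **1. Reproduce the plan's own figure (section 2.8).** With SD = 0.96, d = 0.5, two-sided alpha 0.05 and power 80%:

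n = 2 × 0.96² × (1.960 + 0.842)² / 0.5² = 57.87, so 58 per group. With 10% non-response, 58 / 0.9 = 64.4, so 65 per group.

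The stated 65 is reproduced with a design effect of exactly 1. The calculation takes teachers as independent although the sampling is called cluster sampling.

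**2. Inputs for the error rate.** From the protocol: 130 teachers, eight schools, so m = 130/8 = 16.25 per school; two-sided 5%. Assumed, because the documents do not give them: four schools per arm, and an ICC of the change between 0 and 0.10.

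**3. Formula.** Design effect DE = 1 + (m − 1) × ICC. The true type I error of a teacher-level test is about 2 × [1 − Φ(1.96/√DE)]. At ICC 0.05, DE = 1 + 15.25 × 0.05 = 1.763, √DE = 1.328, 1.96/1.328 = 1.476, and the error is 0.140.

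**4. Simulation.** Change = school effect + teacher error, 4 v 4 schools of 16 or 17 teachers, 20,000 runs per ICC.

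| ICC of change | DE | Type I error, formula | DiD test on teachers, simulated | Paired t within one arm, simulated | t-test on school means, simulated |
|---|---|---|---|---|---|
| 0 | 1.000 | 0.050 | 0.050 | 0.051 | 0.052 |
| 0.01 | 1.153 | 0.068 | 0.069 | 0.066 | 0.052 |
| 0.02 | 1.305 | 0.086 | 0.086 | 0.083 | 0.051 |
| 0.05 | 1.763 | 0.140 | 0.140 | 0.137 | 0.054 |
| 0.10 | 2.525 | 0.217 | 0.223 | 0.220 | 0.050 |

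In this model a nominal 95% interval covers 1 − type I error, or about 86% at ICC 0.05. With 10% loss (m of about 14.6) the formula gives 0.066, 0.082, 0.131 and 0.202 for ICC 0.01 to 0.10, so a somewhat smaller school changes little.

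**5. The other reading of allocation.** With the same data but teachers split between arms within each school, the teacher-level test rejects 0.051, 0.049, 0.049, 0.047 and 0.042 of the time for ICC 0, 0.01, 0.02, 0.05 and 0.10. There is no inflation.

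**6. Power of a valid test.** For the t-test on school means (6 df under 4 v 4), with all 130 analysed, a difference of 0.5 and 0.96 taken as the SD of the change, simulated power is 0.70, 0.63, 0.59, 0.46 and 0.35 for the same ICCs.

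**The case against.** **Allocation by school is inferred.** No section says it, and section 2.7.2 can be read the other way. This stands. It makes the conclusion conditional, and the conflict with the schools that section 2.2.2 assigns to the control group becomes part of the point. The school reading is still the better supported: a lottery of teachers into arms fits poorly with a design described as quasi-experimental and chosen because randomization is not feasible.

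**The plan does not say that the teacher is the error unit.** The covariate list is open-ended, the analysis figure is not available, and a fuller analysis plan could add a school term. This also stands in part. But the article does more than stay silent. It names the tests, the DiD covariates and the protection against type I error, sizes the study with a design effect of 1, and lists its limitations in the Discussion without mentioning clustering.

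**The listed tests are not all the arm contrast.** This is correct. A reader might infer that every named test examines whether schools differ in change rather than whether the intervention works. The documents do not support that. The DiD term still targets the arm contrast, with a standard error that is too small. The paired t-test and McNemar test address change within an arm, and chi-square addresses associations. The pre-post tests matter here because section 2.14.1 offers them as evidence of the intervention's influence.

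**Drift between schools is already conceded.** The Discussion admits weak support for parallel trends and residual confounding. That covers bias from how schools were chosen. It does not cover the random school variation missing from the standard error.

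**Conclusion.** The point holds conditionally. The protocol is inconsistent on whether schools or teachers are allocated, and this must be reconciled. If schools are allocated, the analyses named in section 2.14.2 do not deliver the stated 5% level or 95% intervals for any positive ICC of change. The excess is modest at ICC 0.01 (about 7%) and large at 0.10 (about 22%). These sizes rest on an assumed 4 v 4 split, about 16 teachers per school and an assumed range of ICC. That school size is slightly above the protocol's average of 15, before eligibility criteria are applied.

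A reader might conclude that the trial's inference is invalid as it stands. The documents do not support this without the condition, because under allocation within schools the problem vanishes.

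**What to change.** In section 2.14.2:

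- State the unit of allocation, and bring sections 2.2.2 and 2.7.2 into agreement with it.
- If the unit is the school, estimate the arm contrast in change by one of:
  - a linear mixed model on change scores with a random school intercept and Satterthwaite or Kenward-Roger degrees of freedom;
  - a two-period DiD model with a school-by-time random effect and the same correction (a school intercept alone would not capture variation in change there);
  - a t-test on school mean changes with degrees of freedom equal to the number of schools minus 2.
- Treat within-arm paired t and McNemar results as descriptive only.
- Restate the power in section 2.8 with an assumed ICC and the number of schools.

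**Cost.** The change is one of wording and method, with no new data. Intervals become wider, and power is below the stated 80%: about 0.70 for the school-means test even at ICC 0, and 0.46 at ICC 0.05. Design effect alone would raise the 65 per group to 75, 85, 115 or 164 at ICC 0.01, 0.02, 0.05 or 0.10 (58 × DE, rounded up, then divided by 0.9 and rounded up), before any allowance for few degrees of freedom. None of this removes confounding from the purposive choice of schools, which should stay among the limitations.

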Additionally, the study will be a quasi-experimental study design, specifically the difference-in-differences (DID) quasi experiment, with one intervention and one control group. The DID analysis helps to determine the impact of the intervention by measuring the change in the outcome variable over time and doing a comparative analysis between the intervention and control groups. It helps evaluate the existence and strength of a causal relationship, especially in situations when a randomized controlled trial cannot be implemented, either due to ethical reasons or lack of resources to carry out these trials. For the DID design to accurately determine the causal relationships, it assumes that both the control and intervention groups adhere to ‘parallel trends’ to each other if the intervention did not exist (33). Difference in difference studies are used frequently to assess the intervention impact in a population group, therefore it aligns with our study’s objectives. In these studies we compare the difference in outcomes between the intervention and control groups, which depicts the factors that change overtime within these groups. We analyze two differences in these experiments; the first difference is the before and after comparison in the intervention group, which tells us what factors remain the same over time despite the implemented intervention. The second difference is between the control and intervention group, which tells us what factors were influenced or changed by the intervention over time.

Our study will include a baseline assessment of all study variables, in both intervention and control group, to address the parallel trends assumptions of the DID study design. This will help establish baseline equivalence across both groups on all variables prior to intervention implementation. Although, the study only has one pre-intervention time point, this baseline similarity will strengthen the plausibility of parallel trends. Furthermore, any observable differences will be statistically adjusted for through regression modeling. This will help control any potential confounding factors in the study. For substantial baseline imbalance across key covariates, propensity score weighting will be applied within the DID framework to enhance internal validity. This approach is widely used in DID quasi experimental design studies where multiple pre-intervention points or randomization is not feasible (34).

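### Entered as main effects, age, income and education cannot adjust a two-wave DiD estimate, and the named tests of change do not use the control arm

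*Protocol article*

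**What the plan says.** All references are to the protocol article.

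- **Design (2.1).** The study is "specifically the difference-in-differences (DID) quasi experiment, with one intervention and one control group". The authors acknowledge that "the study only has one pre-intervention time point". Section 2.2.2 has both arms assessed at baseline and endline, so there are two waves.
- **Regression adjustment (2.1 and 2.14.2).** Section 2.1 promises that "any observable differences will be statistically adjusted for through regression modeling". Section 2.14.2 specifies: "Variables such as age, household income, education level, will be included as covariates in the DiD analysis". The reason follows: "This will help adjust for baseline differences between control and intervention groups".
- **Weighting (2.1, repeated among the limitations in the Discussion).** Propensity score weighting is added within the DiD if baseline imbalance is substantial. No threshold is given. The limitations concede that residual confounding may remain.
- **Tests of change (2.14.2).** "Paired samples t-test will be used to compare the pre and post intervention values of continuous" variables, with McNemar's test for categorical ones. Section 2.14.1 says that the comparison of baseline with endline data is meant to show what the intervention did to risk factors, knowledge and practices. Chi-square tests and regression are also listed.
- **Account of DiD (2.1).** In the explanation of the two differences, "the first difference is the before and after comparison in the intervention group, which tells us what factors remain the same over time". The second difference is described as the one between the control and intervention groups.

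**The concern.** Schools are chosen purposively (2.7.1), so the causal claim rests heavily on the DiD contrast and on adjustment for whatever still differs between arms. The plan expects the listed covariates to remove baseline differences. In a DiD, a stable difference in level is not the threat, because differencing removes it. The threat is that teachers of different age, income or education would have changed at different rates without the intervention. Covariates entered as main effects do not address that. An analyst who follows the text in the obvious way would report an adjusted DiD whose point estimate equals the unadjusted one, and readers would believe that confounding had been handled.

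The named tests of change add a second route to a wrong conclusion. A pre-post test within the intervention arm cannot separate the intervention from drift shared by both arms. Teachers are also screened for risk factors, including BMI and waist thresholds (2.7.2, Table 1). If the screening measurements double as baseline, which the article does not state outright, some apparent improvement in teachers who qualified on those measurements would be regression to the mean.

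**Working it through.** **Reproducing the plan's own figure.** Section 2.8 gives SD 0.96, difference 0.5, two-sided alpha 0.05, power 80% and non-response 10%.

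n = 2 × 0.96² × (1.960 + 0.842)² / 0.5² = 57.87, so 58 per arm; 58 / 0.90 = 64.4, so 65 per arm.

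This matches the stated 65. The sample size is not in question here; it supplies the 58 and the 0.96 used below.

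**Why main effects leave the estimate unchanged.** Let G be arm (0/1), T be wave (0/1) and X a covariate fixed per teacher:

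y = a + bG + cT + dGT + gX + error

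1. Replace T by T − 0.5. The coefficient d does not change.
2. The columns 1, G and X are constant within a teacher. The columns (T − 0.5) and G(T − 0.5) sum to zero over a teacher's two rows.
3. The two blocks are therefore orthogonal, and d is estimated from the second block alone: d = (mean change, intervention) − (mean change, control). X plays no part.
4. Age that rises equally for everyone is X plus a multiple of T, so the result is the same.

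The conditions are a linear model, both waves for every analysed teacher, covariates fixed per person, and no covariate-by-time term.

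**What is left uncorrected.** The remaining bias is the sum over covariates of (between-arm difference in the covariate) × (its slope on change). The article gives none of these quantities, so the following inputs are assumed.

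| Covariate | Arm difference | Slope on change | Product |
|---|---|---|---|
| Age | 2 years | 0.08 per year | 0.16 |
| Income | −10 units | −0.008 per unit | 0.08 |
| Education (higher level) | 0.20 | 0.20 | 0.04 |
| Sum | | | 0.28 |

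With a true effect of −0.5, the expected unadjusted estimate is −0.5 + 0.28 = −0.22. Halving the slopes gives a bias of 0.14, doubling them gives 0.56, and with no slope or no imbalance it is 0.

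Simulation with these inputs (65 per arm, SD of change 0.96, 400 replicates, true effect −0.5):

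| Analysis | Mean DiD estimate |
|---|---|
| No covariates | −0.216 |
| Covariates as main effects | −0.216 (largest difference in any replicate 2 × 10⁻¹³) |
| Covariate-by-time terms, or change regressed on arm and covariates | −0.485 |
| Propensity-weighted DiD | −0.479 |

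With 10% endline loss and completers only, the identity still holds (−0.212 both ways). If dropouts' baseline rows are kept, the covariates move the estimate by 0.03 on average and 0.15 at most, but the bias stays: mean −0.199 without them and −0.200 with them.

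**Pre-post tests.** Take 0.96 as the SD of change, which section 2.8 does not say. The paired standard error is 0.96 / √58 = 0.126. For a drift D with no intervention effect, the chance of p < 0.05 is about Φ(D / 0.126 − 1.96).

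| Assumed drift (kg/m²) | Chance of significance in the intervention arm |
|---|---|
| 0.10 | 12% |
| 0.20 | 35% |
| 0.35 | 79% |
| 0.50 | 98% |

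Running the same test in the control arm does not cure this. Comparing two p-values is not a test of the difference between the arms' changes.

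**The case against.** The strongest reply is that the article does not fix the model. Saying that variables are included as covariates in the DiD analysis is compatible with regressing the change score on arm and covariates, which is the remedy proposed here. Model form is commonly left to the statistical analysis plan, and the figure summarising the analysis plan is not available. Income might also be recorded at both waves, and the linear identity does not carry over exactly to logistic models. All of this stands, and it makes the result conditional. It does not rescue the stated reason: a DiD needs no covariates to remove fixed baseline differences, and a reader given that reason would most naturally add main effects.

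Three stronger readings are tempting, and the article does not support them.

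- *That the plan has no working control of confounding.* Propensity weighting within the DiD is planned and does change the estimate. It is triggered only by substantial imbalance; below that, regression is the only adjustment.
- *That every effect test is a pre-post test in one arm.* The DiD is itself a between-arm contrast, the abstract promises comparisons between arms, chi-square and regression are listed, and the paired tests are not restricted to one arm.
- *That section 2.1 never describes DiD correctly.* An earlier sentence there does speak of measuring change over time and comparing it between arms. Only the later account of the two differences goes wrong.

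Regression to the mean is likewise mainly a problem for the within-arm tests. Both arms pass the same screening, so the DiD should largely cancel it.

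**Conclusion.** The point holds in conditional form. In a linear two-wave DiD with complete pairs, person-fixed covariates entered as main effects change the point estimate by exactly zero. This is algebra and rests on no assumed effect size. The purpose that section 2.14.2 gives for them is therefore wrong on its natural reading, and the one other statistical control applies only under an undefined degree of imbalance. Separately, the paired t and McNemar tests do not use the control arm, although section 2.14.1 treats baseline-to-endline comparison as evidence of what the intervention did. The explanation of the two differences in section 2.1 does not state the difference between the arms' changes.

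The sizes (a bias of 0.28 against a true −0.5, and false-positive rates of 12% to 98%) illustrate assumed imbalances, slopes, drifts and an assumed SD of change. They are not properties of this trial, and the actual bias could be nil.

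**What to change.** 1. Define the effect as the difference between arms in baseline-to-endline change.
2. For continuous outcomes, regress each teacher's change on arm plus age, household income and education as measured at baseline (equivalently, include covariate-by-time terms). Fix this list in advance, whatever imbalance is observed. Keep propensity weighting as planned.
3. For binary outcomes, use the arm-by-time contrast as well, for example from a GEE or mixed logistic model.
4. Label within-arm paired t and McNemar results as descriptive, and amend section 2.14.1 to match.
5. In section 2.1, rewrite the two differences as the change within each arm, followed by the difference between those changes. In section 2.14.2, say that the covariates address differences in trend, not fixed differences in level.

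The cost is a few sentences and one model specification. No extra data are needed, and the change-score regression is ordinary linear regression.
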